**3. AIMS/OBJECTIVES/HYPOTHESES**

*Aim*

To compare the treatment efficacy of anorectal biofeedback (clinical indicators and physiological parameters) performed with a novel home-based device with conventional therapy options in patients with functional defecation disorders.

*Faecal incontinence is a heterogeneous condition, there is no single parameter to adequately define or represent an optimal way of assessing clinical outcomes. A range of subjective and physiological measures of bowel function are used as outcomes measures.*

*Site 1 Specific* - A feasibility assessment at Site 1 will evaluate the accuracy and repeatability of the prototype (V2) against anorectal manometry*

1. *Evaluate the capability of experimental device to generate anorectal exercise profiles*
2. *Compare the accuracy of experimental device against anorectal manometry*

*Site 1 and Site 2*

*Subjective primary outcome measures*

1. *Vaizey and Wexner faecal incontinence scores*
2. *Faecal incontinent episodes (days per week)*

*Objective primary outcome measure*

1. *Anal sphincter squeeze pressure (mmHg)*

*Secondary outcome measures*

1. *Anal sphincter resting pressure (mmHg)*
2. *Patient’s own view of effectiveness rating (“worse”, “same”, “improved”, or “cured”) and rating of that change in an ordinal scale of – 5 to + 5*
3. *Frequency of bowel motions and symptoms*
4. *[Experimental device group] Usability interview – 1. Ease of use, 2. Clarity of instructions, 3. Ease of cleaning, 4. Any additional Issues*

Hypotheses

We hypothesised that instrumented home BF therapy with the novel device is as efficacious as clinic-based BF therapy

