**5.3 Data source and Population**

*Study population and size*

The Site 1 feasibility study will be a pilot study involving n=15 (n=20 with 33% dropout) participants per group. This study will evaluate the capability of the experimental device to provide instrumented BF (create distinct BF exercise profiles and is understood by the user) and compare the data against anorectal manometry. This is similar to our previous study [18] but will use the new prototype (V2) and be in a patient population.

The data from this site will not be analysed together with data from Site 2, given the differences in methodology. However, data from Site 1 will be used to improve the statistical analysis plan for Site 2. Currently, the power calculations for Site 2 are based on a previous study [19], but data from Site 1 will be integrated to improve the calculation of sample size and power for Site 2.

Site 2 sample size and power calculations

Based on a previous study of biofeedback treatment for faecal incontinence [19], we estimate that for assessing home-BF and clinic-BF efficacy with a sample size of 30 per group (n=40 with 33% dropout), the paired t-test at the 0.05 significance level can detect a mean change in anorectal function measure of at least 0.45 SD with 0.80 power. This corresponds to at least a mean decrease of 8 in Vaizey/Wexner faecal incontinence score, decrease of 0.6 in faecal incontinence episodes, and 40% increase in anal sphincter squeeze pressure.

For the non-inferiority study, based on changes in the primary outcome measures, with n=30 per study arm, the test for non-inferiority has 0.70 power to reject, at the 0.05 significance level, the null hypothesis that the mean change due to home-BF is smaller than clinic-BF by at least 0.44 SD in favour of he alternative hypothesis that mean changes due to home-BF is no more than 0.44 SD lower than clinic-BF (i.e. Ho: ΔHB-ΔOB<−0.44SD vs. Ha: ΔHB-ΔOB≤−0.44SD).

Using estimates from previous study [19], we consider home-BF no worse than or better than clinic-BF if the home-BF group had at least 9 point decrease in Vaizey/Wexner faecal incontinence score (11 for clinic-BF, SD=3), 0.95 days/week decrease in faecal incontinence episodes (1.1 for clinic-BF, SD=0.25), and 19 mmHg increase in anal sphincter squeeze pressure (25 mmHg for clinic-BF, SD=10).

*Data collection/Outcome measurements*

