**Site 1 and 2 analysis**

The manometric parameters (maximum anal sphincter squeeze pressure (mmHg) and mean anal sphincter resting pressure (mmHg)) for the period before treatment would be compared against parameters after treatment. Clinical indicators Vaizey/Wexner faecal incontinence score, faecal incontinence episodes (days/week), frequency of bowel motions & symptoms, and patient’s own view of effectiveness rating will be analysed. Univariate analysis (paired t-test or Wilcoxon) will be used to evaluate manometric parameter changes, while chi square test will be used to compare clinical indicators.

Non-inferiority study analysis described in Section 5.3 will be used to determine if null hypothesis is accepted or rejected.

***
[figure not shown]
***

***Figure 3.*** *Summary of study procedure*

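### Section 5.8 assigns a chi-square test to the incontinence score and incontinent days per week, two primary outcomes that Section 5.3 sizes as mean changes

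*Protocol*

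**What the plan says.** **Protocol Section 3** names "Vaizey and Wexner faecal incontinence scores" and incontinent days per week as the subjective primary outcomes for both sites. Anal squeeze pressure is the objective primary outcome.

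**Protocol Section 5.3**, the Site 2 sample size text, treats these outcomes as means. With 30 evaluable per group, "the paired t-test at the 0.05 significance level can detect a mean change in anorectal function measure of at least 0.45 SD" with power 0.80. It then translates this into the clinical scales: "This corresponds to at least a mean decrease of 8 in Vaizey/Wexner faecal incontinence score", with matching figures for episodes and squeeze pressure. The non-inferiority test is also set on mean change, with a margin of 0.44 SD and stated power 0.70. Reference changes and SDs are given for the score (11 points in clinic, 9 accepted at home, SD 3) and for episodes (1.1 and 0.95 days per week, SD 0.25).

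**Protocol Section 5.8**, Data analyses, Site 1 and 2 analysis, says three things in sequence:

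- what the clinical indicators are: "Clinical indicators Vaizey/Wexner faecal incontinence score, faecal incontinence episodes (days/week), frequency of bowel motions & symptoms, and patient’s own view of effectiveness rating will be analysed";
- which tests apply: "Univariate analysis (paired t-test or Wilcoxon) will be used to evaluate manometric parameter changes", "while chi square test will be used to compare clinical indicators";
- what decides the hypothesis: "Non-inferiority study analysis described in Section 5.3 will be used to determine if null hypothesis is accepted or rejected".

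**The concern.** Section 5.8 gives the mean-change tests to manometry alone and sends every clinical indicator to chi-square. Two of those indicators are primary outcomes that Section 5.3 sized with a paired t-test and a test on mean change. An analyst cannot follow both sections.

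A chi-square test needs categories. On a score or a days-per-week value it must use either one cell per observed value, which is far too sparse at 30 per arm, or a cut-point, which the protocol does not define. Applied to before and after readings within an arm, it would also treat paired values as independent.

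At stake is how the subjective primary outcomes are reported. If the cut-point is chosen late, it can be chosen with the data in view. If a between-arm chi-square result is non-significant, it may be read as showing that the home device is no worse, which a test for difference cannot show.

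**Working it through.** **1. The sections side by side**

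| Outcome | Role (Section 3) | Sized in Section 5.3 as | Univariate test in Section 5.8 |
|---|---|---|---|
| Vaizey/Wexner score | primary | mean change | chi-square |
| Incontinent days per week | primary | mean change | chi-square |
| Squeeze pressure | primary | mean change | paired t-test or Wilcoxon |
| Resting pressure | secondary | not sized | paired t-test or Wilcoxon |
| Bowel frequency and symptoms | secondary | not sized | chi-square |
| Worse/same/improved/cured rating | secondary | not sized | chi-square |

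The first two rows conflict. Bowel frequency is also a count given an unsuitable test. The last row is categorical, and chi-square suits it.

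**2. The plan's own power figures**

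*Paired t-test, 0.45 SD, n = 30, stated power 0.80.* The noncentrality is 0.45 × √30 = 2.465. By the normal approximation, one-sided 0.05 gives Φ(2.465 − 1.645) = 0.79 and two-sided 0.05 gives Φ(2.465 − 1.960) = 0.69. The noncentral t values are 0.78 and 0.66. The stated figure is therefore approximately right as a one-sided test. Two-sided, it appears only with the 40 enrolled (0.79).

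*Non-inferiority, 0.44 SD, n = 30 per arm, stated power 0.70.* With one-sided 0.05 and no true difference, Φ(0.44/√(2/30) − 1.645) = Φ(1.704 − 1.645) = 0.52. This does not reproduce. It is a separate matter and does not affect the present point; both calculations confirm that Section 5.3 is built on means.

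**3. Cost of a between-arm chi-square test**

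Inputs from Section 5.3: 30 per arm, SD 3, and a difference of 2 points (11 − 9), which is 0.667 SD. A second difference of 2.2 points (0.733 SD) is used because a two-sided t-test then has power 0.80. Assumptions: normal changes, a split at the pooled median, two-sided 0.05, no continuity correction.

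With d the difference in SD units, the proportions above the cut are p1 = Φ(d/2) and p2 = 1 − p1. The standard errors are se0 = √(0.25 × 2/30) = 0.1291 under no difference and se1 = √(2·p1·p2/30) under the alternative. Power = Φ[(p1 − p2 − 1.96·se0)/se1].

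- 2 points: p1 = 0.631, p2 = 0.369, se1 = 0.1246. Power = Φ[(0.261 − 0.253)/0.1246] = **0.53**, against **0.72** for the t-test.
- 2.2 points: p1 = 0.643, p2 = 0.357, se1 = 0.1237. Power = Φ[(0.286 − 0.253)/0.1237] = **0.61**, against **0.80** for the t-test.

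Simulation with integer-valued changes (8,000 trials per setting) gave 0.53 and 0.60 for the split, and 0.71 and 0.79 for the t-test. The loss is about 19 percentage points, roughly a quarter of the t-test's power.

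Chi-square on the raw score values, one cell per value, gave 0.12 and 0.15. It had about 14 categories and about 94-95% of expected counts below 5, so it is not a valid use of the test.

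**4. What a non-significant chi-square would mean**

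If the home arm is truly worse by 2 points, the limit of what Section 5.3 accepts, the median-split test is non-significant with probability 1 − 0.53 = 0.47. If the cut is set at the clinic arm's median instead, the figure is 0.49. About half of such trials would show no significant difference, so that result says nothing in favour of non-inferiority.

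**The case against.** The strongest reply is that the sentence after the chi-square rule hands the decision on the hypothesis to the Section 5.3 non-inferiority analysis, which is on mean change in the primary outcomes. The confirmatory test is therefore not a chi-square test. This stands. A reader might infer that the plan cannot show non-inferiority on these outcomes; the documents do not support that. Chi-square alone cannot show it, but the plan as a whole still can.

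A reader might also infer that most of the planned power is lost. Between arms, that holds only for the one-cell-per-value reading, which no analyst should use. A median split costs about a quarter.

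Larger losses can be produced for a before/after chi-square within an arm. With an effect chosen to give the paired t-test power 0.80 (0.529 SD), a median split has 0.55, 0.42 and 0.23 at pre-post correlations of 0.3, 0.5 and 0.7. Those correlations and that effect are assumptions. On Section 5.3's raw figures, with the SDs taken as SDs of change, the within-arm effects are 8/3 = 2.7 SD and 0.6/0.25 = 2.4 SD; both tests then have power near 1. These figures illustrate the problem but do not measure it.

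It can also be said that a cut-point belongs in the SAP. Leaving one to the SAP would be ordinary if the protocol were silent on the test. It is not silent: it names a test for these primaries that differs from the one it sized. An SAP using mean changes within arm would depart from Section 5.8; one using chi-square would depart from Section 5.3.

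Finally, chi-square does suit the categorical effectiveness rating. The rule is too broad rather than wrong throughout.

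**Conclusion.** The conflict is real and concerns two primary outcomes. Section 5.8 assigns chi-square to the incontinence score, incontinent days per week and bowel frequency; Section 5.3 sizes the first two as mean changes.

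The non-inferiority test on mean change remains in the plan. The defect therefore has two parts:

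- The within-arm paired analysis that Section 5.3 sized for the score and episodes is replaced by chi-square. If chi-square is meant only between arms, these outcomes have no within-arm test named in Section 5.8.
- The between-arm comparison of the same primaries gets a second, less powerful test, with no rule on which counts if they disagree.

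The power loss cannot be fixed to one number, because it depends on a categorisation that the protocol does not give. The fall from about 0.72-0.80 to 0.53-0.61 rests on 30 evaluable per arm, normal changes with SD 3 and a median split.

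This should be fixed before analysis. It does not by itself invalidate the trial's main conclusion.

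**What to change.** In Section 5.8, Site 1 and 2 analysis:

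1. Limit chi-square to categorical indicators, such as the worse/same/improved/cured rating.
2. State that the Vaizey score, the Wexner score, incontinent days per week and bowel frequency are analysed as changes on their own scale, with a paired t-test or Wilcoxon within arm.
3. For the primary outcomes, state that the between-arm difference in mean change, with its confidence interval, is compared with the Section 5.3 margin, and that this comparison carries the non-inferiority conclusion.

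Step 3 needs one margin. Section 5.3 gives 0.44 SD, which is 0.44 × 3 = 1.32 points on the score, but its raw-unit criterion allows 11 − 9 = 2 points. That discrepancy is a separate matter, to be settled at the same time.

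The cost is a few sentences of protocol wording, with no new data, visits or patients. Nothing is lost for the categorical items, which keep the test they have now.

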**5.7 Consent Process**

[name] (site 1) and [name] (site 2) will obtain written consent from eligible participants or delegate the duty to [name] (site 1 and 2). Consent will be sought on the day of their study after potential participants have been give project information and opportunity to discuss the study with an investigator. It will be made clear that participation is voluntary and that the participant may withdraw at any stage with no detriment to their health care. Investigator will gauge their understanding by asking the potential participants questions about what they believe they are being asked to do. Investigators will also address any questions that arise from the participants in regards to the study. If the participants have any concerns or questions that arise at any stage in the future, they may contact [name] to further discuss them. Formal consent will be obtained in writing immediately following this as the information sheet and consent form is read by/to the participant, who may then indicate their voluntary participation by signing the consent form. A copy of the consent and information sheet will be provided to the participant to keep.

Participants may wish to withdraw from the study at any time. In the event the participant wishes to withdraw from the study, we will retain all data collected up to the point with withdraw.

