2. **Squeeze and hold:** The patient is asked to squeeze the anus for as long as possible, for a maximum of 30 seconds. By convention, this manoeuvre is performed three times. Both the maximal contractile pressure and endurance times are measured. Ideally, rectal pressure should not increase, because that would imply the patient has contracted the abdominal wall.
3. **Simulated defecation (push):** The patient bear down as if to defecation and attempt to expel the catheter. This manoeuvre should produce sufficient rectal propulsion pressures with simultaneous anal sphincter relaxation (>20% relaxation).

During treatment period, patients are asked to keep a bowel and food diary. During their in-clinic visits, the therapist will provide consultation on the patient’s progress and any changes to clinical indicators.

*Home-based biofeedback using new device*

In addition to the general instructions, patients selected for home-based BF with novel device (**Group B**) will be trained on the use of home-training device by the therapist. For feasibility study at Site 1, participants will use the device in the clinic under supervision for a maximum of six sessions.

Accuracy and repeatability of prototype V2 will be assessed in the first five (n=5) group B participants. Participant manometry parameters (e.g. resting, push, squeeze) will be compared against the prototype data during their first training session. Capabilities of the V2 sensors will compared against previous V1 data [18] to determine if the V2 prototype is suitable for use. If V2 sensors are not deemed suitable, the trial will be temporary suspended while the technical issues are resolved. During this time, the participant will be removed from the study and begin conventional treatment. If V2 sensors are suitable the participant will continue with trial and subsequent sessions.

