Group B participants will undergo 6 supervised clinic sessions with the experimental device. After session two, they may also take the device home and continue training during the treatment period. The wireless device contains sensors to measure anal sphincter and rectal pressures. A condom sheath is placed over the probe before it is inserted into the anal canal. The user will download the training program (mobile app) onto their mobile phones, which will guide the user through the required exercises (identical to the clinic-based BF manoeuvres listed above). Participants will be asked to insert the probe and perform training for 5 – 10 minutes daily over a training period of 2 months. Training data is send to a cloud server for therapist to monitor compliance and correct usage. The participants are asked to keep daily bowel and food diaries on the app, this information is sent to the cloud accessible only by the therapist and investigators.

Upon completion of the feasibility study, home-based BF with novel device at Site 2 (Group B) will only undergo one supervised training session with the novel device. Participants then take the device home and continue training unsupervised for the duration of their treatment period. The therapist monitor adhesion remotely through the cloud server and will arrange fortnightly telehealth consultations to provide encouragement and evaluate progress.

At the end of the treatment period, participants in Group B will undergo a short useability interview. The therapist will ask the participant questions regarding the 1. Ease of use, 2. Clarity of instructions, 3. Ease of cleaning, 4. Any additional Issues.

*Data analyses*

At the end of the treatment period participants will return to the clinic for a repeat anorectal manometry study to determine changes in anorectal physiology parameters. The therapist will also review their bowel and food diaries. The therapist will discuss the results with the participants and plan the next course of action.

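### Non-inferiority on incontinent days per week is planned as one change score in about 30 of 40 per arm, with no stated use for the diary weeks of those who stop; a repeated-measures analysis of all randomised Site 2 participants would be a cheap improvement

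*Protocol*

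**What the plan says.** Section 3 lists faecal incontinent episodes, in days per week, as a primary outcome. Section 5.3 sizes Site 2 on a "sample size of 30 per group (n=40 with 33% dropout"). It frames the non-inferiority test as "based on changes in the primary outcome measures, with n=30 per study arm", and adds "the test for non-inferiority has 0.70 power to reject, at the 0.05 significance level", with a margin of 0.44 SD. The Site 1 and 2 analysis paragraph in Section 5.8 returns to that test: "Non-inferiority study analysis described in Section 5.3 will be used to determine if null hypothesis is accepted or rejected". The same paragraph counts incontinent days per week among the clinical indicators and assigns those a chi square test.

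On data collection, Section 5.8 says of the clinic arm "During treatment period, patients are asked to keep a bowel and food diary" and of the home arm "The participants are asked to keep daily bowel and food diaries on the app". Treatment lasts 2 months in both arms. On withdrawal, Section 5.7 says "we will retain all data collected up to the point with withdraw".

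The protocol describes no repeated-measures analysis and does not say how the retained diary data of those who stop will be used.

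**The concern.** A diary kept over 2 months can give up to about 8 weekly values per person. A single pre-to-post change uses only the ends of that series and only people who reach the end. Those who stop have early diary weeks that show how they were responding, and the test as described has no place for them.

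This matters more in a non-inferiority comparison than in most. At Site 2 the home arm trains unsupervised after one session, while the clinic arm attends up to six sessions. Section 2 puts poor adherence to biofeedback down to difficult access and invasiveness, and home treatment changes the first of these. Reasons for stopping may therefore differ between arms. If home users who see no early benefit stop, the remaining home users look better than the arm as randomised, and the error favours the device.

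**Working it through.** **Inputs from the protocol.** 40 per arm enrolled, 30 analysed, stated dropout 33%, margin 0.44 SD, alpha 0.05 (sidedness not stated; one-sided used here), SD of the change in days per week 0.25 (Section 5.3).

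**The plan's own figures.**
- Power: Φ(0.44/√(2/30) − 1.645) = Φ(1.704 − 1.645) = 0.52, not the stated 0.70. That is a separate matter, but it shows there is no power to spare.
- Dropout: 30 × 1.33 ≈ 40 gives the enrolment figure. However, 30 of 40 is a 25% loss, and a true 33% loss leaves 40 × 0.67 ≈ 27. Both are carried below.
- Margin: 0.44 × 0.25 = 0.11 days/week. The same section also gives 1.1 − 0.95 = 0.15 days/week, which is 0.15/0.25 = 0.6 SD.

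**Analytic check.** Let a fraction d of the home arm stop, and let stoppers do g SD worse than home completers. The home completer mean then exceeds the home-arm mean by d × g. With random stopping in the clinic arm and home truly worse by exactly the margin, false non-inferiority is Φ(d·g/√(2/n) − 1.645). The margin cancels, so this holds for 0.44 SD or 0.6 SD. If the selection sits in the clinic arm instead, the sign of d·g reverses.

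| d | n per arm | g | d·g (SD) | home only | clinic only |
|---|---|---|---|---|---|
| 0.25 | 30 | 0.25 | 0.062 | 8% | 3% |
| 0.25 | 30 | 0.5 | 0.125 | 12% | 2% |
| 0.25 | 30 | 1.0 | 0.25 | 25% | <1% |
| 0.33 | 27 | 0.25 | 0.083 | 9% | 3% |
| 0.33 | 27 | 0.5 | 0.165 | 15% | 1% |
| 0.33 | 27 | 1.0 | 0.33 | 33% | <1% |

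Example: 0.125/√(2/30) = 0.484, and Φ(0.484 − 1.645) = 0.123. With equal selection in both arms the terms cancel and the rate is 5%.

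**Simulation of the diary.** The documents give no diary correlation or dropout pattern, so these are assumptions: 40 per arm, a week-0 value plus 8 weekly values, within-person correlation 0.5, home truly worse by 0.44 SD of the change, and 10 per arm stopping after week 3. Stopping is random in the clinic arm and related to poor early response in the home arm.

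| Correlation of stopping with early response, home arm | Completer change score | Repeated measures, all weeks |
|---|---|---|
| 0.38 | 10% | 5% |
| 0.63 | 16% | 5% |
| 0.85 | 21% | 4% |

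- With 13 of 40 stopping and the strongest selection, the completer score gives about 25% and repeated measures about 5%.
- With equal selection in both arms the completer score gives about 5%; with clinic-only selection, about 1%.
- With random stopping both methods hold about 5%, and repeated measures gains roughly 3 to 6 points of power.

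**A second set-up**, with one mid-treatment value correlated 0.5 to 0.85 with the final one and 25% or 33% home-selective dropout, gives the completer score a bias of 0.11 to 0.37 SD (0.03 to 0.09 days/week at SD 0.25) and 11% to 42% false non-inferiority. An estimate that also uses the stoppers' earlier values gives 5% to 6%.

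**The case against.** The strongest reply is that the protocol never says the stoppers' weeks are thrown away. A reader might infer that from 30 of 40, but that figure is a sample-size allowance and defines no analysis set; Section 5.7 keeps the data; and missing-data rules may sit in an analysis plan not shown. This stands. The documents support only that no use is stated.

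A reader might also take the change score to be the only test of this outcome. It is not: the analysis paragraph also assigns it a chi square test, which conflicts with Section 5.3. Chi square would not use the stoppers' weekly series either, so the point survives, but the conflict must be resolved with it.

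Third, the weekly data may not be fully in hand. Section 5.3 lists diary content as bowel habits, stool consistency and symptoms; it names neither incontinent days nor a pre-treatment diary period. Diaries may be on paper, and the only diary review tied to final assessment is at the end-of-treatment visit, which stoppers may miss. This stands and shapes the fix.

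Fourth, home-only selection is assumed, and no figure in the documents supports that direction. Selective loss of poor responders from the clinic arm would work against the device. The good behaviour of the repeated-measures model also follows partly from making stopping depend on recorded values. Both stand as limits on the size.

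Finally, Section 5.3 joins the thresholds for score, episodes and squeeze pressure. If all must be met, a false pass on this outcome alone would not carry the trial. That limits the consequence but does not protect this comparison.

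**Conclusion.** The point holds as a worthwhile, low-cost improvement. Section 5.3 describes non-inferiority on a single change with about 30 of 40 per arm and gives no role to diary weeks that both arms are asked to record and that are retained after withdrawal.

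The inflation is conditional. It is about 10% to 21% false non-inferiority with 10 of 40 stopping, if selection on poor early response occurs only in the home arm. It is near 5% if selection is equal in both arms and below 5% if it occurs only in the clinic arm. The tempting conclusion that this trial will produce false non-inferiority is not supported: the selection pattern, its strength and the diary correlations are all assumptions. What is supported is that the described comparison is exposed to an imbalance the trial could largely correct from the diary, provided stopping depends on recorded values.

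**What to change.** In Section 5.3 and the Site 1 and 2 analysis paragraph of Section 5.8:

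1. State that incontinent days per week is derived from the bowel diary in both arms, and that diaries of those who stop, including paper ones, are collected.
2. Analyse weekly values from all randomised Site 2 participants, using every diary week up to withdrawal, with a mixed model for repeated measures: arm, week, arm-by-week and baseline. Test the home-minus-clinic difference at the last treatment week.
3. Use a baseline recorded before treatment starts. The first on-treatment diary week is not suitable, because it follows randomisation and adjusting for it can remove part of the treatment effect.
4. Replace the chi square test for this outcome.
5. Reconcile the two margins (0.44 SD, or 0.11 days/week; and 0.15 days/week, or 0.6 SD) before any test is run.
6. Keep the completer change score as a sensitivity analysis, and add one that gives home-arm stoppers a worse course.

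The cost is wording and slightly more analysis work, with no extra participants. If no pre-treatment value is currently recorded, one must be defined and collected. The model assumes that stopping depends on recorded values, which is why step 6 is needed.
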